### ***Control arm***

No study-supported activities will be conducted in control communities during the active intervention phase. Women who give birth in these communities during the active intervention period will not be registered nor contacted by study volunteers nor receive study-generated reminders. No participants will be screened or enrolled in the control arm communities during the active intervention time period.

### ***Endline Survey***

To assess the reach of the program platforms as well as the relative effectiveness of the reminder and incentive-based activities, we will conduct an endline survey at the end of the six-month active study implementation phase, in each of the two intervention areas (10 communities each) and in the control area (5 communities) which did not receive any study-related interventions.

Surveyors will visit all households in the 15 communities and will identify households in which a woman who has given birth in the previous 12 months resides. If no household member is available at the time the surveyor visits, or a household member is available and reports that a birth occurred in the previous 12 months but that the mother is not currently available, the surveyor will return to the household up to two additional times to attempt to make contact. If any member of the household requests that the surveyor not return, this will be noted and no future visits will be conducted. If a potential participant or screened and enrolled participant requests that the surveyor return at another more convenient time, the surveyor will return up to two additional times to attempt to complete the screening and enrolment or the interview process.

**All women who reside in the community and have given birth in the previous 12 months will be eligible to participate in the endline survey.** Among eligible women, surveyors will describe the purpose and procedures of the survey and ask if the woman is available and interested in participating. If the woman is interested, the surveyor will guide her through the informed consent process. If the woman

is unavailable at this time, surveyors will return to the household up to two additional times to attempt to make contact and/or complete the survey. If the woman provides informed consent (see *Informed Consent Endline Survey*), the surveyor will engage in a brief interview with the woman using a structured survey tool, with data captured on an electronic tablet.

The survey will collect demographic and socioeconomic information about the household and the woman, basic information about the birth, vital status, and vaccination history of children. For each recent birth (within the previous 12 months), detailed vaccination reports will be collected. Vaccination history and date of birth will be based on nationally standardized health cards and vaccination cards if available, and maternal report if written documentation is unavailable. A modified version of the vaccination survey form developed for the Demographic and Health Surveys will be used to collect vaccination-related information. This vaccination survey module combines information from the child health card with maternal self-reports, and is widely used for national and international comparisons (see *Endline Questionnaire* attached).

Surveyors will be trained and sensitized regarding respectful and compassionate communication to prepare them for how to interact with a woman who reports the death of a newborn. Surveyors will refer woman who have lost a child to relevant local support resources as available and appropriate.

The interview will be conducted at the household at a room or location selected by the enrolled participant. Measures will be taken to attempt to identify a quiet and semi-private area free of distractions and with relative confidentiality. Surveyors will inform the woman that they are interested only in her experience and not the input of others and that there are no “right” or “wrong” answers to the survey. A woman may request to be accompanied during the interview by a friend, neighbor or household member of her choice if she so prefers. Surveyors will be conversant in local languages and the survey will be conducted in the language of choice of the respondent.

The survey will take approximately 10-15 minutes to complete. No costs will be incurred for enrolled woman for participating in the endline survey and no compensation or incentives will be offered.

Screening, enrollment, and data collection in the endline survey activity is independent of screening, enrollment and data collection in the intervention activities (reminders Group A and incentives Group B).

### **Primary and secondary outcomes**

The primary study outcome is completion of early vaccination; we will consider a child as having successfully completed the early vaccination schedule if **the child has received the BCG vaccine and at least one dose of the polio vaccine within four weeks (28 days) after delivery**. We will additionally report the vaccine-specific coverage and the average age at vaccine receipt for each vaccine in each of the three arms.

The secondary outcome of the study will be the percentage of births identified via endline household survey that are reported by study volunteers. This outcome will be of particular interest for Ghana’s Birth and Death Registry, which is currently making major efforts to increase registration coverage in this region.

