### Rationale & background information

Despite major progress made in vaccination coverage overall, timeliness of vaccines remains a key concern in many settings [1, 2]. In Ghana, 95% of children receive BCG vaccination within the first two years of life [3], but only about half of these children receive the vaccine within the first 30 days after delivery, and more than 25% receive the vaccine more than 6 months after birth [3]. Early vaccination coverage is particularly low in settings where a large share of women deliver at home, as it is the case in Ghana’s Northern region, where only a minority of women seek out facilities for delivery [3]. According to the latest estimates, less than 50% of children in Ghana’s Northern region receive Bacillus Calmette–Guérin (BCG) vaccines within the first three months of their life, and less than 40% get polio vaccination, exposing a large number of infants to these diseases [2].

Recent research conducted in this region shows that the large majority of households have access to mobile phones now even in the most rural areas [4]. The main idea of the proposed project is to use these mobile phone networks to simultaneously address two of the biggest bottlenecks in vaccine delivery: timely registration of births, and lack of maternal effort to get essential vaccines. Evidence from India

suggests that even small rewards can often result in substantial increases in vaccine uptake [5] – we will test this hypothesis using mobile networks in rural areas of Northern Ghana.

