### **Sample Size Calculation**

According to the latest Demographic and Health Survey from Ghana, about 50% of children in the Northern region receive both Bacillus Calmette–Guérin (BCG) and Polio vaccines within the first 30 days after delivery. We hypothesize that this proportion can be increased to 80% with either intervention

(reminder-only and incentives). Assuming 20 children in each cluster, and an intra-class correlation coefficient ( $\rho$ ) of 0.05, a sample size of 100 children is required in each active treatment arm (reminder-only and incentives) and in the control communities for comparison, to achieve power 0.9 at alpha 0.05. With a crude birth rate of 40, we expect 20 births in each community within six months of baseline for the average village with a population of 1000, which means that the targeted sample size for the active treatment program (100 per active treatment arm) should be achieved in less than six months.

The endline survey will be conducted in all communities in the three arms and will attempt to enroll all women who delivered a newborn in the previous 12 months. This will additionally allow us to compare outcomes of interest across treatment groups and in the pre- initiation and study intervention periods. We anticipate this will include approximately twice the number of births expected in the 6-month intervention period (600). To account for woman who may have been missed during the intervention period, refused to participate, or moved into the community after initiation, we propose a maximum of 750 woman for the endline survey.

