### **Study Duration and Follow-Up**

The two interventions will be implemented for six months in 10 pre-selected villages. During the six-month intervention period community volunteers will be engaged in recording all births in the catchment areas of the study communities.

The duration of participation for enrolled participants in each of the intervention arms will be approximately two weeks (soon after birth through two weeks of newborn life), with possible limited follow-up through 30 days of newborn life at the latest.

**Reminder arm (Intervention Group A):** Enrolled mothers will receive up to four voice or text messages to remind them of the importance and recommended timing of newborn vaccinations, starting from soon after birth and continuing through the first 10 days of newborn life (at approximately birth, 3, 7 and 10 days of life as appropriate). All contact with mothers will be completed by 30 days of newborn life at the latest.

**Incentive arm (Intervention Group B):** Enrolled mothers will receive contact and encouragement from community volunteers to complete newborn vaccinations, and volunteers will contact women to attempt to document vaccination status starting from soon after birth and continuing through the first 10 days of newborn life, with possible follow-up for encouragement and verification. All contact with mothers will be completed by 30 days of newborn life at the latest.

After the intervention period ends in both active treatment arms (30 days after the enrollment of the last participant in each of the 2 active intervention arms), an endline survey will be conducted in all 15 communities (10 intervention arm communities and 5 control arm communities).

**Endline survey:** During the endline survey period all households in the communities will be visited by a household surveyor over an estimated two-month period. Each interview is expected to take approximately 10-15 minutes.

No further contact with subjects in any of the three arms will be conducted after the completion of the endline survey.

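### The average age at vaccine receipt covers only infants already vaccinated at the survey, so it does not measure timeliness over all infants and can understate or reverse a benefit

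*Protocol*

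**What the plan says.** The Protocol, Primary and secondary outcomes, defines the primary outcome as a yes/no status by a fixed age: "the child has received the BCG vaccine and at least one dose of the polio vaccine within four weeks (28 days) after delivery". An infant not vaccinated by then counts as a failure and stays in the denominator. The same section adds two further measures by arm: vaccine-specific coverage and "the average age at vaccine receipt for each vaccine in each of the three arms". It gives no rule for infants without a receipt date.

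The data come from one cross-sectional survey. Under Endline Survey, "All women who reside in the community and have given birth in the previous 12 months will be eligible to participate in the endline survey", and "For each recent birth (within the previous 12 months), detailed vaccination reports will be collected". Under Study Duration and Follow-Up, "all households in the communities will be visited by a household surveyor over an estimated two-month period". Age at interview therefore runs from about 0 to 12 months.

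Two comparisons are planned. Sample Size Calculation says that the survey will allow the team to "compare outcomes of interest across treatment groups and in the pre- initiation and study intervention periods".

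On background timing, Rationale & background information reports that nationally 95% of children receive BCG within two years, that about half of these receive it within 30 days, and that "more than 25% receive the vaccine more than 6 months after birth". Sample Size Calculation takes it that "about 50% of children in the Northern region receive both" vaccines within 30 days, and hypothesises a rise to 80%.

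**The concern.** Age at receipt exists only for infants vaccinated before the interview. Being vaccinated is a post-randomisation event that both interventions try to bring about, so the arm means are taken over differently selected infants and randomisation does not protect the contrast. If an intervention brings in infants who would otherwise have been unvaccinated at the survey, their ages enter its mean and nothing matching enters the control mean.

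The second problem is truncation. An infant interviewed young can contribute only an early age. Where two groups differ systematically in age at interview, their means differ even if the vaccination schedule is the same.

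Timeliness is the trial's declared topic, and this is its only continuous measure of timeliness. The pilot is meant to inform a larger study or government programmes, so a misleading mean would be carried forward.

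**Working it through.** **Inputs from the protocol.** Coverage by 30 days of 50% (control) and 80% (intervention); national BCG timing; birth window of 12 months. These coverage figures do reproduce the stated sample size: 52 per arm × design effect (1 + 19 × 0.05 = 1.95) = 101.4, against 100 stated. The protocol gives no figure for average age.

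**Assumptions.** Ages are uniform within each interval named below. Age at survey is uniform over 0 to 365 days unless stated. The observed mean is E[age at receipt | age at receipt ≤ age at survey].

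**1. Few late control vaccinations.** Control: 50% at days 0–14 and no others. Intervention: the same 50%, plus 30% at days 14–28. Before truncation:
- control: 7.0 days
- intervention: (0.50 × 7 + 0.30 × 21) / 0.80 = 9.8 / 0.80 = 12.25 days

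With truncation by age at survey: 7.0 against 12.1 days. No infant was vaccinated later and day-28 coverage rose by 30 points, yet the mean is 5 days worse.

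**2. As 1, with a further 5% at days 30–180 in both arms.** 13.1 against 15.9 days.

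**3. Late catch-up.** Control: 50% at days 0–28, 10% at days 30–180, 35% after one year. Intervention: 60%, 30% and 5%. Means: 24.7 against 36.5 days.

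**4. National-like timing.** Control: 47.5% at days 0–28 (half of 95%), 23.75% at days 30–180, 23.75% at days 180–730. Intervention: 30 points move from the two late groups to days 14–28. Means: 43.0 against 24.8 days. There is no reversal.

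**5. Understatement.** Take nearly the same national curve (late interval from day 183) with survey ages of 30–273 days. The control mean is about 37 days. A 30-point gain at days 14–28 brings it to about 24 days if the movers come proportionally from all infants not vaccinated early. It comes to only about 32 days if they come solely from infants who would have been unvaccinated at the survey. The day-28 gain is identical, but the shift in the mean is about 13 or about 5 days.

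**6. Where the reversal stops.** Let q be the share of control infants vaccinated late but before the survey, m their mean age, and r the fraction of them still late in the intervention arm. The means are equal when

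(3.5 + qm) / (0.5 + q) = (9.8 + rqm) / (0.8 + rq).

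- m = 105, r = 0: 92.75q = 2.625, so q = 0.028
- m = 60, r = 1: 11.7q = 2.1, so q = 0.18

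Across these assumptions the reversal disappears once q reaches about 3% to 18%.

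**7. Age at survey alone.** Apply the control schedule of step 4 to everyone. The mean is 30.8 days for infants aged 30–210 days at survey and 56.5 days for those aged 210–365 days, a difference of 25.7 days. A hand check at the mid-points of the two ranges:
- day 120: (0.475 × 14 + 0.1425 × 75) / 0.6175 = 28.1 days
- day 287.5: (0.475 × 14 + 0.2375 × 105 + 0.0464 × 233.75) / 0.7589 = 55.9 days

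**8. The alternative measure.** Restricted mean time unvaccinated to day 28, over all infants:
- scenario 1: control 0.5 × 7 + 0.5 × 28 = 17.5; intervention 0.5 × 7 + 0.3 × 21 + 0.2 × 28 = 15.4
- scenario 3: control 0.5 × 14 + 0.5 × 28 = 21.0; intervention 0.6 × 14 + 0.4 × 28 = 19.6
- scenario 4: control 0.475 × 14 + 0.525 × 28 = 21.35; intervention 0.475 × 14 + 0.3 × 21 + 0.225 × 28 = 19.25

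It ranks the arms correctly in all three, including the two in which the mean age reverses.

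**The case against.** **The reversals rest on invented timing.** This stands in part. Under the protocol's national BCG pattern the mean moves the right way, so a reader who infers that the better arm will appear to vaccinate later goes too far. The protocol does not settle which pattern applies. Its regional figures (about 50% with both vaccines by 30 days, under 50% with BCG by three months) leave little room for catch-up between days 30 and 90, which is the condition that favours a reversal. They come from different cited sources, however, and say nothing about months 3 to 12.

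**Age at survey does not bias the arm comparison.** This stands. All arms share the birth window and the fieldwork period, and villages are randomised, so truncation acts alike in expectation. A reader might infer from the long national tail that censoring alone distorts the arm contrast; the design does not support that. The comparison of periods is different, because intervention-period births are necessarily younger at interview.

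**Coverage is reported beside the mean.** True, and it would alert a careful reader. It does not repair the mean as a measure of timeliness.

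**Restriction to vaccinated infants is inferred, and a SAP could define the handling.** The restriction is not written out, but it follows from the measure named. A SAP could add censoring rules, but it would then be estimating something other than an average age at receipt.

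**The measure is minor.** It is neither the primary nor the named secondary outcome. That limits the consequence to interpretation.

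**Conclusion.** The point holds in a limited form. The arm means of age at receipt are taken over infants selected by the outcome and do not measure timeliness over all infants. They can understate a benefit (a shift of about 5 rather than 13 days for the same 30-point gain). They can reverse one (7.0 against 12.1 days) when late vaccinations seen in the control arm fall below about 3% to 18% of infants. With national-like timing they point the right way. In the comparison of periods, an identical schedule would favour the intervention period by about 26 days.

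All these sizes rest on assumed distributions of age at receipt; only the coverage levels and the broad national timing come from the protocol. Nothing here calls the primary outcome, its test or the sample size into question.

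**What to change.** In Primary and secondary outcomes, replace the average age at receipt, or keep it only as a descriptive figure labelled as being among vaccinated infants. Report for each vaccine, by arm and by period, one or both of:

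- the cumulative proportion vaccinated by age (Kaplan–Meier), with infants not vaccinated censored at age at interview, or at age at death for those who died;
- the restricted mean time unvaccinated to day 28. The survey starts 30 days after the last enrolment, so all infants enrolled in the intervention programmes have passed day 28 by then; births after that enrolment may be censored earlier.

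Give intervals that allow for clustering by village.

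The cost is a change of wording and a little analysis. Dates of birth and vaccination and vital status are already within the survey's scope. The one real addition is a stated rule for vaccinations known only from maternal report without an exact date. The day-28 restricted mean overlaps with the primary outcome, but it adds how early within the 28 days vaccination occurred.

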### **Research Hypotheses (H1-3)**

H1: Nudging mothers through voice and text messages will increase early vaccination coverage.

H2: Nudging mothers through community volunteers and small rewards will increase early vaccination coverage.

Given that birth registration remains low in many parts of Ghana, we will also test a new community-based reporting model, under which volunteers appointed by the community will receive small rewards for reporting births in their communities. We will test the extent to which such a program improves birth reporting and registration:

H3: Providing small mobile-phone based incentives to volunteers selected by communities will result in accurate and timely reporting of births in rural areas.

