### *Community Volunteer Appointment and Birth Registration*

In all of the 10 intervention arm communities, we will implement sensitization meetings at the beginning of the study to explain the purpose and objective of the proposed work. We will then ask the community to appoint a local birth registration volunteer. Minimum qualifications for the local birth registration volunteer include the following: female; owns and has daily access to a smart phone with camera capability and the knowledge and ability to take photos and send SMS messages; is a member of the local community and in good standing with the community; speaks the local language fluently and has at least a minimum working knowledge of English and Dagbani; can read and write (local language fluency and working knowledge of English).

Candidate volunteers will be informed of the expectations of participating in the project, the project duration (6 months), the expected time commitment per week (approximately one hour per week in the incentive program areas and 30 minutes per week in the reminder-only program areas). They will then be invited to accept or decline the appointment as a birth registration volunteer. Birth registration volunteers who accept the appointment will undergo a standardized training to further inform them of the procedures and expectations of their role, and to provide practical advice on successfully engaging in their role.

Community volunteers will be expected to document and report all births in their communities to a central phone hotline which will be managed by study personnel. To motivate volunteers to report all births in their communities, and to compensate them for their efforts, they will be given a 2 cedis reward (USD 0.50) for each birth reported during the active study duration (6 months).

**Intervention arm A (“reminders only”)** focuses on automated voice and text messages sent to mothers. In this treatment arm, community volunteers will register all births in the community as described above.

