### **Data Management and Statistical Analysis**

All data will be captured electronically, and processed in the IPA Ghana office. Data will be stored at a password-protected and encrypted data server. Ongoing day-to-day data management and quality assurance will be conducted by IPA. Data will be shared with the PI ([name]) and his research team members at Swiss TPH during data collection for intermittent quality assurance purposes, and at completion of field work a de-identified dataset will be shared for involvement in final data cleaning and analysis. De-identified data will be kept by the research team indefinitely for use in future analyses as appropriate. Links between personally –identifiable information and study data will be destroyed after the primary data analysis for the study is complete.

Given the randomized assignment of treatment, it is anticipated that statistical analysis will be relatively straightforward. Logistic regression models will be used to analyze the primary and secondary outcomes of interest. Standard errors will be adjusted for cluster-level correlation using generalized estimating equations with robust variance-covariance estimation [14, 15].

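### As defined, the secondary outcome cannot exceed about 50% even with perfect volunteer reporting, because its denominator runs beyond the months and villages that volunteers covered

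*Protocol*

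**What the plan says.** Under Primary and secondary outcomes: "The secondary outcome of the study will be the percentage of births identified via endline household survey that are reported by study volunteers". The same section names Ghana's birth and death registry as an interested user of the result.

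The Endline Survey section sets the population that feeds the denominator: "All women who reside in the community and have given birth in the previous 12 months will be eligible to participate in the endline survey". All 15 villages are surveyed. The Sample Size Calculation section says that births from before initiation are included on purpose, so that periods as well as arms can be compared.

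Volunteers work in the 10 intervention villages for six months (Community Volunteer Appointment and Birth Registration; Study Duration and Follow-Up), and "they will be given a 2 cedis reward (USD 0.50) for each birth reported". The reward per registered birth is the same in arm B. Of the control villages the protocol says: "Women who give birth in these communities during the active intervention period will not be registered nor contacted by study volunteers".

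The hypothesis that this outcome serves is H3: "Providing small mobile-phone based incentives to volunteers selected by communities will result in accurate and timely reporting of births in rural areas". It is introduced with the aim: "We will test the extent to which such a program improves birth reporting and registration". On analysis, the protocol says: "Logistic regression models will be used to analyze the primary and secondary outcomes of interest".

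**The concern.** A completeness percentage should divide births reported by births that could have been reported. Here the denominator also takes in births from before volunteers were appointed, births after their reporting period ended and, if all villages are pooled, births where no volunteer ever worked. Each counts as a failure to report. A registry official reading the result would conclude that volunteers miss at least half of births even if they missed none.

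Two further problems follow from the same definition. The control arm can only score zero, so it is not a usable comparator. And H3 speaks of accuracy and timeliness, while the outcome records only whether a surveyed birth was reported.

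**Working it through.** **Inputs**
- Average village of 1000 people; crude birth rate 40 per 1000 per year (Sample Size Calculation).
- 15 villages, 10 of them with volunteers (Study Design Overview).
- Survey look-back of 12 months (Endline Survey).
- Volunteer reporting for 6 months; survey from 30 days after the last enrolment, lasting about two months (Study Duration and Follow-Up).

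**1. Reproduce the plan's figure.** Births per village in six months: 1000 × 40/1000 × 0.5 = 20. Over 15 villages: 300. Over 12 months: 600. This matches the stated 600.

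**2. What the look-back contains.** If a woman is interviewed t months after the intervention ends, her 12-month window holds 12 − 6 − t months before volunteers, 6 volunteer months and t months after. With t from 1 to 3, that is 5 down to 3 months before, 6 during, and 1 to 3 after. The volunteer share is always 6/12.

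**3. Ceiling.** Reportable births: 10 × 20 = 200. Denominator in the intervention villages: 10 × 40 = 400, so the ceiling is 200/400 = 50%. Denominator over all villages: 600, so the ceiling is 200/600 = 33.3%. The reported value is the true completeness times the ceiling:

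| True completeness | Reported, 10 villages | Reported, 15 villages |
|---|---|---|
| 100% | 50% | 33.3% |
| 90% | 45% | 30% |
| 80% | 40% | 26.7% |
| 60% | 30% | 20% |

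With the denominator limited to the 10 villages and the six months, it is about 200 births and the ceiling is 100%.

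**4. Control arm in a logistic model.** With no events in control, the control log-odds are log(0), which is minus infinity, so any log-odds ratio against control is infinite. A simulated check used 15 villages of 20 births, control reporting of 0 and an assumed 80% in both active arms. As iterations rose from 5 to 25, the arm coefficient grew from about 8.1 to 28.2 and its standard error from 1.6 to over 35,000. Maximum likelihood did not converge, and the robust GEE standard errors could not be computed. A GEE of A versus B in the 10 volunteer villages fitted normally (log-odds ratio 0.07, standard error 0.33). That run had no within-village correlation, so it shows that the model can be fitted, not how precise it would be.

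**5. Is the reporting incentive randomised?** Arm A pays 2 cedis per birth reported and arm B pays 2 cedis, a difference of 0. Control has neither a volunteer nor a reward. A versus B therefore holds the reporting reward constant, and control has no value of this outcome other than zero.

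**6. What is measured, by section**

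| Section | Property of reporting |
|---|---|
| Research Hypotheses (H3) | accuracy and timeliness |
| Study Design Overview | accuracy and completeness of registration, per arm |
| Primary and secondary outcomes | reported or not, i.e. completeness |

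A volunteer report that matches no surveyed birth enters neither the numerator nor the denominator of the defined percentage. The delay from birth to report does not enter it either.

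**The case against.** The best defence is that the restriction is implied. The protocol gives its reason for the 12-month window (comparing periods), and the survey collects date of birth, so a sensible analyst would split by period and not blame volunteers for births before their appointment. That shows that the repair is easy, but not that it has been specified: the outcome definition has no limit by date or village, and the survey includes the earlier births deliberately.

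It is also fair that the analysis section names no contrast for this outcome, and that choosing one is commonly left to the SAP. A reader might infer that the planned logistic regression cannot be fitted at all. The protocol does not support that: only a model that includes control fails, and A versus B or a simple proportion can be computed.

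A reader might also infer that payment per report leaves false reports unchecked, so that over-reporting would pass as success. The protocol does not support that either. It assigns the implementing partner verification as well as distribution of the volunteers' birth-registration incentives, though it does not describe the check. Nor is accuracy absent from the protocol, since the Study Design Overview mentions it. What stands is that the defined outcome does not capture it, and that no stated outcome covers timeliness.

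Finally, H3 can be read as a performance claim about one programme in a pilot. That reading is workable, but the stated aim of testing how far reporting improves implies a comparator that this outcome does not have.

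**Conclusion.** The outcome is wrong as written. Taken literally, it halves volunteer completeness in the intervention villages (ceiling 50%) and cuts it to a third if all 15 villages are pooled (ceiling 33%). The 50% assumes births spread evenly over the year and a survey that starts after the six reporting months have ended and within six months of that end, as planned. It does not depend on the birth rate. The 33% also assumes villages of similar size. The understatement would occur only if the literal definition were applied, but nothing in the protocol directs otherwise.

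Two limits follow. A model for this outcome that includes control has no finite arm estimate, and no randomised contrast tests the reporting incentive, so H3 can be answered only as a description of how well the programme performed.

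This should be fixed, but it does not endanger the trial. It concerns the one secondary outcome of a pilot. The primary outcome's sample size does not use it and reproduces: for 50% versus 80%, two-sided 5% (assumed) and 90% power, (1.96√0.455 + 1.282√0.41)²/0.3² = 51.0 per arm; times 1 + 19 × 0.05 = 1.95, this gives 99.5 against the stated 100.

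**What to change.** - **Denominator:** count endline-survey births dated within the volunteer reporting period in the 10 intervention villages. Do not narrow this to live births, because volunteers are asked to report every birth.
- **Analysis:** report the proportion overall and by active arm with a village-clustered 95% confidence interval. Exclude the control arm from this outcome and keep A versus B descriptive.
- **H3:** state it as a feasibility estimate of the reporting programme, not as an effect of incentives.
- **Reconcile** the hypotheses, the design overview and the outcome definition. As a supporting measure, give the share of volunteer reports matched to a surveyed birth, with the caveat that non-matches include mothers who were absent, refused or had left the village, and so are not all false reports. Report days from birth to report if the hotline logs report dates; this is an assumption, since the protocol does not say so.

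The cost is protocol and SAP wording. Date of birth is already collected, and the current definition already requires volunteer reports to be matched to surveyed births. The matching rules should be set early, because identifiers are removed before analysis and the links are destroyed after the primary analysis.
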